| B. How many participants will take part at institutions covered by this Research Ethics Approval?                                                                                                                                                                                       | 44                                                                                                                                                                                                                                                                                                                                        |                                              |                                        |                                              |  |  |  |
| 7.3. Principal Investigator and Research Team Experience                                                                                                                                                                                                                                | [name] is a Professor in the Department of Psychiatry at the University of British Columbia in Vancouver, Canada. She is a world leader in consumer-involved psychosocial research in bipolar disorders (BD). [name] founded and leads the Collaborative RESearch Team to study psychosocial factors in Bipolar Disorder |                                              |                                        |                                              |  |  |  |

(CREST.BD). CREST.BD's mandate is to advance research, clinical practice, and social change for psychosocial care and supports for BD through a community-based participatory research (CBPR) approach. Regionally, she is the BC SUPPORT Unit's Patient Engagement Methods Cluster Lead (part of the Canadian Strategy for Patient Oriented Research), overseeing a budget of one million dollars to advance patient-engaged research in BC. Additionally, she is the Program Director for the APEC Digital Hub for Mental Health and VP for Outreach for the International Society for Bipolar Disorders.

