| 4.3.B. If applicable, please describe the relationship between this proposal and the previously/ simultaneously submitted proposal listed above.                                                                                                  | 
CREST.BD has successfully utilized digital platforms (e.g., the Polarus App) for self-management knowledge translation (KT). While digital tools represent one promising avenue for BD care, they do not address the needs of all individuals, such as those impacted by the digital divide or facing additional barriers such as physical disability. To support equitable and inclusive access to this information, diverse avenues of delivery are required. One candidate alternative delivery format is face-to-face, peer delivered self-management psychoeducation and support.
 
In H23-01462, we conducted focus groups to inform the creation of a peer-delivered psychoeducation program. Manuals for facilitators and attendees have now been created, drawing on the knowledge base integrated in the PolarUs app.
 
This ethics application corresponds to the administration and a pilot evaluation of the newly developed, peer-delivered psychoeducation program.
 |                                        |                                          |                                        |                          |                           |                                         |     |     |     |     |

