| proposal.                                                                                                                  | administration of the program and a pilot evaluation of the feasibility, acceptability, and efficacy of this program for self-management of BD.                                                                                                                                                                                                                                                                                                                                                                                                                                                                                                                                                                                                                                                                                                                                                                                                                                                                                                                                                                                                                                                                                                                                                                                                                                                                                                                                                                                                                                                                                                                                                                                                                                                                                                                                                                                                                                                                                                                                                                                                                                                                                                                                                                                                                                                                                                                                                                               |

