| 
5.1.B. Summarize the research proposal, including study purpose, hypothesis, study population, and research method.
 | 
Background and Purpose:
 
Peer support (where individuals with shared lived experience of a mental health condition provide each other with informational, emotional, and social support) may be an acceptable way to disseminate information on self-management strategies, capitalizing on the expertise and knowledge of people who live well with BD.
 
Peer-facilitated group psychoeducation includes the benefits of evidence-based self-management information and tools, with the added advantage of providing role models for recovery and modelling of self-management skills (Proudfoot et al., 2012) (Tse et al., 2019). Unfortunately, there is a dearth of BD-specific peer-facilitated self-management psychoeducation programs, and corresponding evaluations of their efficacy.
 
To capitalize on the potential of peer support to enhance the delivery of BD self-management information, content from two, web-based, self-directed psychoeducational interventions was adapted to create a peer-facilitated psychoeducation program using a community-based participatory research (CBPR) framework. The resulting program contains eight, weekly, two-hour sessions. Each session focuses on a topic related to QoL in BD (including Mood, Sleep, Physical Health, Relationships, Money, Self-esteem, and Independence), and contains a combination of education, opportunities for peer-to-peer knowledge exchange, and activities that facilitate practice of self-management strategies. A facilitator and attendee manual have been created for use in this program.
 
Methods:
 
The project will be implemented across two phases:
 
In the first phase, which we have already completed, we have applied CBPR principles to develop a peer-facilitated, QoL-focused group psychoeducation program for individuals with BD. The resulting program, entitled 'Thriving with bipolar disorder' will be delivered in eight, weekly, two-hour sessions that will be co-facilitated by two peer facilitators with lived experience of BD.
 
In the second phase, we will conduct a pilot evaluation of the feasibility, acceptability, and preliminary efficacy of the program. The program will be delivered through Hope+Me, an Ontario-based charity that supports people living with mood and anxiety disorders through education, advocacy, training, and support services. Four peer facilitators will be recruited through Hope+Me and will attend a
 |

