|                                                                               | 
~5.5 hour training session prior to commencing the program. We will aim to recruit 32-40 program participants (8-10 per group) given previous research summarizing the ideal group size (Biggs et al., 2020).
 
The evaluation will be conducted as a single-arm, uncontrolled, pilot feasibility trial. An explanatory sequential mixed-methods design will be used (Creswell & Clark, 2011). The following data will be collected:
 
 
- Participants will provide baseline demographic and clinical information in a Qualtrics survey as part of their consent.
 
- Participants will complete Qualtrics surveys for efficacy measures at baseline, immediately after completing the program and 1 month after completing the program.
 
- Program feedback will be collected from participants immediately after completing the program through a Qualtrics survey.
 
- Peer facilitators will complete a brief, post-session Qualtrics survey each week, recording attendance, fidelity, and session feedback.
 
 
At the end of the intervention period, a subset of consenting participants (~n=12) and peer facilitators (~n=4) will be invited to participate in a one-hour qualitative individual interview over Zoom.
 
Study Population:
 
Four peer facilitators will be recruited through Hope+Me. Inclusion criteria for program participants are: (1) aged 18 or older, (2) a self-reported diagnosis of a mood disorder, (3) sufficient access to an internet-enabled computer or smartphone device through which they can access the Zoom teleconferencing platform, and (4) ability to understand, read and write English, (5) at least one year of prior experience leading peer support groups or recovery programs through Hope+Me, and have previously received training through Hope+Me and (6) have completed a Criminal Record Check (https://rcmp.ca/en/criminal-records/criminal-record-checks).
 
Inclusion criteria for program participants are: (1) aged 18 or older, (2) residing in Canada, (3) a self-reported diagnosis of BD, (4) ability to understand, read and write English and (5) sufficient access to an internet-enabled computer or smartphone device to access the Zoom teleconferencing platform. Exclusion criterion will be the inability to communicate in written and verbal English to a sufficient level to allow participation in the program and research activities.
 |

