| 5.6. Summary of Procedures

Describe briefly in a step-by-step manner what the researcher will be doing with participants, after they have been recruited and consented.                                                                                                                               | 
Facilitators will attend one ~5.5 hour training session provided by [name] to review the program structure, delivery, session-by-session objectives, and use of the facilitator manual. This training will also cover relevant components of the TCPS2 that extend to the facilitator role, including acquiring renewed consent, managing conflicts of interest, and maintaining privacy and confidentiality.
 
Prior and ongoing training and supervision through Hope+Me will allow facilitators to experience an extensive training model with programs such as safeTALK, de-escalation technique training, WRAP® training, ongoing monthly Community of Practice meetings, peer debriefing channels following sessions, and support from experienced peer support group facilitators. Details about these programs are provided in section 6.2 and in the attached documentation titled 'Peer Facilitator Guidelines and Supports'.
 
The program will be delivered virtually using Zoom teleconferencing software. Participants will be sent calendar invites containing the Zoom links for each session, and instructions on how to download and use Zoom. In the week prior to the first session, participants will be provided with a copy of the attendee manual and a link to a Qualtrics form where they will complete baseline efficacy measures.
 
We aim to recruit 32-40 program participants, assigning 8-10 participants per group (for a total of 4 groups). Each group will be co-facilitated by two peer facilitators with lived experience of BD. Each group will attend eight, two-hour sessions each week. All eight sessions follow the same general format: Participants will first enter a welcome area, where they will be introduced to their two group facilitators and another Hope+Me staff member that is on standby, should a client require one-on-one support. The document 'Guidelines for Virtual Groups' (attached in documentation) will be reviewed prior to the group starting. Peer facilitators will present an
 |

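### The attendee manual and the baseline efficacy survey go out together, so nothing ensures that baseline is measured before exposure to program material

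*Protocol*

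**What the plan says.** Section 5.6 (Summary of Procedures) describes one hand-out step, timed to the week before session 1, in these words: "participants will be provided with a copy of the attendee manual and a link to a Qualtrics form where they will complete baseline efficacy measures". It gives no order between the two items and no closing time for the survey.

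The manual is program material. Section 5.1.B states: "A facilitator and attendee manual have been created for use in this program". Section 4.3.B gives its origin: "Manuals for facilitators and attendees have now been created, drawing on the knowledge base integrated in the PolarUs app". Section 5.1.B adds that the program was adapted from two online interventions that people worked through on their own.

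On the measurements, section 5.1.B says: "Participants will complete Qualtrics surveys for efficacy measures at baseline, immediately after completing the program and 1 month after completing the program". On the design it says: "The evaluation will be conducted as a single-arm, uncontrolled, pilot feasibility trial". Efficacy is a stated aim: section 5.1.A describes a "pilot evaluation of the feasibility, acceptability, and efficacy of this program", and section 5.1.B calls the efficacy part preliminary.

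**The concern.** A baseline should describe participants before they meet any part of the intervention. Here the survey and the written self-management content arrive together, so a participant who opens the manual first and answers afterwards is no longer unexposed. Someone who answers after session 1 has been exposed to more still.

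In a controlled trial a comparison group treated in the same way could absorb some of this. Here there is none. The same baseline score enters both change scores, so any shift carries into both. The protocol does not say that it will be recorded when a participant opened the manual, so as planned an affected baseline could not be told from a clean one.

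This is the order of procedures, which the protocol itself fixes. An analysis plan cannot recover a pre-exposure measurement that was never taken.

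**Working it through.** **Step 1: does any other section close the gap?** The sequence, section by section:

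- At consent (5.1.B, 5.4, 6.6), a survey collects demographic and clinical information. The efficacy measures are not part of it; 5.1.B lists them separately.
- In the week before session 1 (5.6), the manual and the baseline efficacy link are provided together.
- Eight weekly sessions follow, then the post-program survey, then the 1-month survey (5.1.B, 5.6).
- Section 6.1 gives the length of the baseline survey (half an hour) but not when it must be done.

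None of these sections puts the survey ahead of the manual or closes it before session 1. None says that participants will read the manual first.

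**Step 2: how a shift would enter the result.** Let f be the share who complete baseline after reading, and s the mean shift that reading causes in their score. Mean observed baseline = true baseline + f × s. Each change is a later score minus baseline, so the bias in both the post-program and the 1-month mean change is −f × s. On a scale where higher is better, early benefit (s > 0) makes the change too small. If reading makes people rate themselves lower (s < 0), the change is too large.

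**Step 3: size.** From the protocol: 4 groups of 8–10 give 4 × 8 = 32 to 4 × 10 = 40 participants. With four facilitators, 40 + 4 = 44, which matches the total in section 7.2. The protocol gives no f, s, SD, pre-post correlation or effect size, so the following inputs are assumptions.

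- Assume f = 0.25 to 0.75 and s = 0.05 to 0.20 SD of the measure. Lowest: 0.25 × 0.05 = 0.0125 SD. Highest: 0.75 × 0.20 = 0.15 SD.
- For scale, the 95% half-width for a mean change is t(0.975, n−1)/√n in SDs of change: 0.361 at n = 32 and 0.320 at n = 40. The normal approximation gives 0.346 and 0.310. These ignore clustering by group and any dropout, both of which would normally widen them.
- The bias is in SDs of the measure and the half-width in SDs of change. With equal SDs at both times, SD of change = SD × √(2(1 − r)), so the units agree only at a pre-post correlation r of 0.5. On that further assumption the bias runs from 0.0125/0.361 = 3% to 0.15/0.320 = 47% of the half-width. A higher r makes the bias count for more, a lower r for less.

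**Step 4: the same question as a share of the true change.** If a share g of the eventual change is already present when a reader answers, observed/true change = 1 − f × g. Illustrative values:

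| f | g | observed/true |
|---|---|---|
| any | 0 | 100% |
| 0.5 | 0.1 | 95% |
| 0.5 | 0.25 | 87.5% |
| 1.0 | 0.5 | 50% |

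The last row is an extreme. Reading alone over about a week would have to deliver half of the eventual change, and in every participant.

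**The case against.** A reader might infer that the pre-post change is contaminated, or that efficacy would be manufactured. The protocol supports neither. It says nothing about who reads what, or when, so it shows only that exposure before baseline is possible. If the survey is answered before session 1, that exposure is at most about a week of optional reading ahead of eight two-hour sessions. Early benefit would work against the program, understating its effect. A change in self-rating could act in either direction, but nothing in the document points to one.

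Section 5.6 also answers a form box that asks for a brief description. The full research protocol, the pre-program survey and the manual are listed in section 9 as separate attachments and are not at hand. Survey instructions or a send order could be set there, and how much stand-alone content the manual carries is inferred from its stated origin.

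The stakes are limited too. This is a pilot, the efficacy aim is preliminary, and no decision threshold in the document depends on the estimate.

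Withholding the manual has a cost of its own. Section 6.2 places the help-resource list in it and lets participants decline any aspect of the program or evaluation, so the manual should not depend on completing a research survey. Discarding late baselines would also lose data from a sample of only 32–40.

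These points lower the severity and shape the remedy. They do not remove the gap: followed as written, section 5.6 allows the only efficacy comparator to be measured after exposure.

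**Conclusion.** The point holds as a weakness in the order of procedures. The protocol does not ensure that the baseline efficacy measures come before access to the manual or before session 1, so both pre-post changes may be biased by an unknown, possibly small amount.

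The range of 0.0125–0.15 SD rests wholly on assumed reading shares and shifts. Only its upper end would be noticeable beside the precision that 32–40 participants allow, and that comparison needs the further assumption r = 0.5. Attendance, fidelity, program feedback and the interviews are untouched, so the feasibility and acceptability aims stand. No sample-size figure changes.

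This should be fixed, because the remedy costs almost nothing and works only before participants receive the manual. The possible bias is not established or large enough to make it a condition for running the study.

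**What to change.** Amend section 5.6 as follows:

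1. Send the baseline efficacy link first. Release the manual when the survey is submitted, or at session 1 at the latest whether or not it was submitted.
2. Ask for submission before session 1, and record the times of submission and of manual release.
3. Keep any baseline completed after manual access or after session 1, flag it, and repeat the change analyses without the flagged records as a sensitivity analysis. Late responders may differ in other ways, so this shows how much the result depends on them and is not a correction.
4. Send the help-resource list separately and without condition, so that the new order does not delay it.

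The cost is two messages in sequence, or an automatic release at the end of the survey, plus one extra mailing for the resource list. No instrument, visit or participant is added. The downside is that slow responders have less time with the manual before session 1.

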at Hope & Me - Mood Disorders Association of Ontario. As the co-chair of the CAN-BIND Community Advisory Committee, he represents the community perspective on the Ontario Brain Institute's Knowledge Translation, Outreach, and Communications team and has been a long-time community advisor with Collaborative RESearch Team to study psychosocial issues in Bipolar Disorder (CREST.BD) and the Centre For Youth Bipolar at CAMH. His interests include patient advocacy, team building, diversity enhancement, and collaboration.

Conflict of Interest Statement: We confirm that none of the study team members will have relationships with program participants/facilitators. Study team members will not be in a position of authority over a participant/facilitator. If any conflict of interest is perceived or arises, the study team member will absolve themselves from participating in recruitment or data collection activities.

## 8. Confidentiality - Behavioural Study [\[View Form\]](#)

### **8.1. Security of Data During the Course of the Study**

All information and data collected will be password-protected and encrypted, and will be accessed only using university-encrypted and owned computers. Audio/video recorded interviews will be transcribed. Electronic data files will be stored on UBC's secure OneDrive server. Any data shared with Co-Investigators will be done through UBC OneDrive and will be de-identified and password-protected. Interview recordings will be transcribed by a transcription service. Audio/video recorded interviews conducted using Zoom will be downloaded locally to the interviewer's computer and immediately transferred to a secure UBC server. Psychoeducation program sessions will not be recorded, nor will any participant-completed activities (e.g., worksheets, etc.) be collected. Information collected by Hope+Me for their standard operating procedures (e.g., program registration forms and group peer support summaries) will be password-protected and encrypted, and will be accessed only using Hope+Me owned computers by approved staff.

All research questionnaires (surveys, consent form, demographic questions) will be administered via Qualtrics using our university Qualtrics account. Qualtrics is designed to gather sensitive questionnaire data online, and it incorporates a number of procedures for minimizing risk of a breach of confidentiality. We will set up our data collection so that IP addresses are not stored. Qualtrics servers are protected by high-end firewall systems, and vulnerability scans are performed regularly. Complete penetration tests are performed yearly. All services have quick failover points and redundant hardware, and complete backups are performed nightly. Our electronic dataset will be de-identified, encrypted, password protected, and will only be accessible by core research team members. The electronic data will be kept on password-protected accounts and will be transferred to a limited number of

|                                                                                                                                                                  |                                                                                                                                                                                                                                                                                                                                                                                                                                                                                                                                                                                                                                                                                                                                                                                                                                                                                                                                                                                                                                                                                                                                                                                                                                                                                                                                                                                                                                                                                                                                                                                                                                                                                                                                                                                                                                  |
|------------------------------------------------------------------------------------------------------------------------------------------------------------------|----------------------------------------------------------------------------------------------------------------------------------------------------------------------------------------------------------------------------------------------------------------------------------------------------------------------------------------------------------------------------------------------------------------------------------------------------------------------------------------------------------------------------------------------------------------------------------------------------------------------------------------------------------------------------------------------------------------------------------------------------------------------------------------------------------------------------------------------------------------------------------------------------------------------------------------------------------------------------------------------------------------------------------------------------------------------------------------------------------------------------------------------------------------------------------------------------------------------------------------------------------------------------------------------------------------------------------------------------------------------------------------------------------------------------------------------------------------------------------------------------------------------------------------------------------------------------------------------------------------------------------------------------------------------------------------------------------------------------------------------------------------------------------------------------------------------------------|
|                                                                                                                                                                  | university-owned and -maintained computers of [name]. No research data will be transferred to Hope+Me.                                                                                                                                                                                                                                                                                                                                                                                                                                                                                                                                                                                                                                                                                                                                                                                                                                                                                                                                                                                                                                                                                                                                                                                                                                                                                                                                                                                                                                                                                                                                                                                                                                                                                                                |
| 8.2. Access to Data                                                                                                                                       | The UBC study team and research staff will have ready access to the data. A transcription service located in Canada will be given access to de-identified audio files only for the purposes of working on interview transcriptions.                                                                                                                                                                                                                                                                                                                                                                                                                                                                                                                                                                                                                                                                                                                                                                                                                                                                                                                                                                                                                                                                                                                                                                                                                                                                                                                                                                                                                                                                                                                                                                                              |
| 8.3. Protection of Personal Information                                                                                                                   | 
Program evaluation surveys completed by facilitators and participants will not collect any personally identifying information (e.g., names, contacts, etc.). Data from surveys will not be made available to facilitators and participants during the research study to minimize bias in the results.
 
We will record audio (and, if participants join via the Zoom videoconferencing platform, video) data of the (optional) qualitative interview, however this will not be linked or stored with identifiable data.
 
Any personally identifying information (e.g., name, postal code and emergency contact information) collected by Hope+Me to register for the program is strictly part of standard operating procedures and will only be used in the event of an emergency. All identifying information will only be accessible to the on-call Hope+Me staff member providing one-on-one support for program activities, and will be destroyed upon completion of the program.
 
We have three major types of identifiable data: (a) contact information (names, email address, and phone number), (b) consent forms and (c) demographics and clinical information. Each of these data files will be stored separately from research data, only being linked through a subject ID number - the file containing this list will be password protected, encrypted and stored separately from the data.
 
Participant data will be kept confidential, except for certain information that we must report, such as abuse of a child, to the RCMP as part of our professional duty. Additionally, if the research team has concerns about participant responses to survey or interview questions, we reserve the right to reach out to Hope+Me to enquire about their participation in the program.
 |
| 8.4. Transfer of Data

Will any data be transferred (made available) to persons or agencies outside the lead University or Health Authority? | yes                                                                                                                                                                                                                                                                                                                                                                                                                                                                                                                                                                                                                                                                                                                                                                                                                                                                                                                                                                                                                                                                                                                                                                                                                                                                                                                                                                                                                                                                                                                                                                                                                                                                                                                                                                                                                              |

| If yes, describe in detail what information will be released, to whom, how the data will be transferred, how and where it will be stored and what safeguards will be used to protect the identity of participants and the privacy of their data. Attach the data transfer agreement if applicable. | 
Co-investigator [name] is based at Monash University, in Melbourne, Australia. Data will be shared through UBC OneDrive and will be de-identified and password-protected. If a copy of the data will need to be stored on a local computer for analysis, the data will be stored through Monash Network Storage, managed by eSolutions and stored on servers owned by Monash University. All data on these servers is automatically backed up by the University, requires a VPN to access when off-site, has restricted access options and is encrypted.
 
Additional information about Monash University's data security protocols can be found through this link:
 
https://www.monash.edu/library/researchers/data-collection-management/guidelines/storage
 |                   |                          |      |                          |                   |   |             |                        |                   |   |                   |                        |                   |   |                   |                        |
|-----------------------------------------------------------------------------------------------------------------------------------------------------------------------------------------------------------------------------------------------------------------------------------------------------------|-------------------------------------------------------------------------------------------------------------------------------------------------------------------------------------------------------------------------------------------------------------------------------------------------------------------------------------------------------------------------------------------------------------------------------------------------------------------------------------------------------------------------------------------------------------------------------------------------------------------------------------------------------------------------------------------------------------------------------------------------------------------------------------------------------------------------------------------------------------------------------------------------|-------------------|--------------------------|------|--------------------------|-------------------|---|-------------|------------------------|-------------------|---|-------------------|------------------------|-------------------|---|-------------------|------------------------|
